### Protocols for intervention adaptation (specific aim 1)

2.2.

#### Qualitative investigation with NHPI participants and experts

2.2.1.

Older adult participants will be recruited from our past trials of hula for hypertension, along with hula instructors and providers who treat NHPI with cognitive impairment. We will convene three focus groups with 15 NHPI aged 50 and older who participated in one of our past hula intervention projects. There are no other inclusion criteria. The only exclusion criterion is the presence of a significant cognitive problem (i. e., diagnosed dementia) that may prevent a participant from fully understanding the consenting process and the questions. Eligible participants will respond to semi-structured questions about their experiences with hula for health promotion (benefits, barriers), their thoughts about its use for physical, social, and cognitive engagement, and their recommendations for enhancing the social and cognitive aspects of the intervention for older NHPI. Each focus group will last about 90 min and be co-facilitated by a member of our investigative team and a peer educator from the CBO hosting the group. Each focus group participant will be provided a gift card valued at $25 as remuneration. It is not a requirement for these older adult participants to have SCI or MCI because the primary purpose of conducting these focus groups is to yield information to ensure the physical aspects of hula can accommodate the range of physical capacities for older adults.

Semi-structured key informant interviews will be conducted with four geriatricians, nurses, and/or other providers of local healthcare systems who care for NHPI with dementia. Also, four hula experts from the participating CBO who have experience with our hula intervention will be interviewed to elicit advice regarding the use of hula for improving cognitive function in older NHPI. ADRD advisors and hula experts will be provided information on the intervention curriculum and its efficacy in treating hypertension before interviews. They will be asked their opinions on the intervention components; their effects on exercise, social, and cognitive engagement; their importance in preventing ADRD; and any recommendations for enhancing the intervention for adults with memory problems. The hula experts will be asked how to maintain the cultural integrity of the intervention while enhancing retention and its social and cognitive components through hula-specific strategies. Each participant interviewed will be provided a gift card valued at $50 as remuneration.

#### Qualitative data analysis

2.2.2.

Framework analysis will be used to analyze findings (Klingberg et al., 2024). It is a structured approach to analyzing qualitative data, often used in health research, and useful when researchers have specific questions to generate practical insights from interviews and focus groups. Focus groups and interviews will be audio recorded for transcription by trained transcribers and analyzed along with field notes. A transcript-based, investigator-derived framework method to analyze focus group discussions and interviews will extract common themes, ideas, and recommendations and organize them into categories developed *a priori* (Gale et al., 2013). At least two research team members with hula expertise, Hawaiian cultural training, and/or qualitative research experience will separately review transcripts to identify items for the general domains of the framework and then repeat data, noting those that occurred with high frequency. They will meet to collaboratively review the information extracted and establish an agreement on key information provided and their appropriate domain in the framework. An investigator with Hawaiian cultural and hula expertise will review the transcripts to determine if additional information and/or domains could be identified or clarified. These findings will be used to refine the hula intervention. The final protocol will be reviewed and approved by the Steering Committee.

### Protocols for group-randomized trial (specific aim 2)

2.3.

#### Target population and recruitment

2.3.1.

After intervention adaptation, we will recruit NHPI aged 50 and older with SCI or MCI and at least 1 modifiable vascular or metabolic risk factor. Inclusion criteria: 1) self-reported NHPI ancestry, 2) age 50–75 years, 3) SCI or MCI, 4) diagnosis of hypertension, diabetes, dyslipidemia, or obesity measured at enrollment, 5) willing and able to engage in the moderate physical activity necessary for hula, and 6) physician’s approval to participate in moderate physical activity. These specific inclusion criteria are intentional as this is the optimal age range for preventing future dementia in people with cognitive impairment. Those above 75 years old are not likely to benefit from this study, given their advanced age. Exclusion criteria: 1) actively practicing in hula at least weekly, 2) normal cognition and no subjective cognitive complaints, 3) diagnosed ADRD (mild to severe), or 4) currently diagnosed major depressive disorder at moderate or greater stage.

The recruitment sites will adhere to the same recruitment strategy, and each site will recruit participants for up to two hula cohorts (16 total with concurrent intervention and control cohorts at each site). CBO staff will use their records to identify potentially eligible NHPI based on client registries and/or lists of past recipients of services. They will be contacted by mail or by phone to inform them about the study and asked to contact the CBO research coordinator if they are interested in participating. CBO staff will also set up information booths at events (e.g., health screenings and cultural gatherings). People who approach the booth will be given a card similar to that mailed to potential participants in step 1, with the option of completing the brief screening. Individuals interested in participating will complete a brief screening form to determine preliminary eligibility, which will include questions about a family history of ADRD, any previous clinical MCI or ADRD diagnosis, and having noticed or been told by others that their memory is getting worse or that they are getting “more scattered.” Endorsing at least one of these items will meet the requirements for further screening to determine SCI or MCI eligibility.

#### Informed consent and screening

2.3.2.

Potentially eligible participants will be scheduled for an in-person enrollment visit at the CBO, at their home, or at another location that offers sufficient privacy to conduct the interview. At this visit, we will verify the presence of at least 1 qualifying vascular risk factor. For high blood pressure, diabetes, and dyslipidemia, participants will be asked to either produce a pill bottle or other proof of a current prescription or to consent to have study staff verify the diagnosis through their healthcare provider. For obesity, we will measure height and weight to verify a body mass index ≥30 kg/m^2^. The Research Coordinator will then review the study’s goals, procedures, and requirements for participation. Written informed consent will include a box that participants can initial to indicate their understanding that final enrollment depends on confirmation of criteria for a vascular risk factor and SCI or MCI.

To date, there are no published cognitive assessment tools validated for NHPI. Since it is not yet possible to use biomarkers as the clinical gold standard to assess the presence of ADRD in individuals, a combination of three assessment tools was used to assess an individual’s cognitive performance. To screen for SCI/MCI, staff will first administer the Cognitive Change Index (CCI), a subjective measure of cognitive impairment (Rattanabannakit et al., 2016). It contains 20 questions scored on a 0–4 Likert scale (range 0–80), with higher scores representing more subjective memory complaints. Scores ≥6 will indicate prevalent SCI. Second, staff will administer the Quick Dementia Rating System (QDRS), a validated staging assessment for ADRD of participants’ self-reported ratings of cognitive function (Galvin, 2015). Ratings are based on the extent and severity of change from prior abilities in 10 domains such as Memory and Recall, Decision Making/Problem Solving, and Activities Outside the Home. Scores range from 0 to 30 and will be categorized using established thresholds (0–1.5 = normal; 2.0–5.5 = MCI; 6.0–12.5 = mild ADRD; 13.0–20.5 = moderate ADRD; ≥21 = severe ADRD) (Galvin, 2015). Third, the NSCT will be administered, a brief 90-s executive task that incorporates attention, planning, and set-switching. The scoring is from 1 to 70, using the number of correct answers. The test uses a cut-off score of 36 or greater to indicate normal cognitive function. Fourth, the 2-item PHQ (Irwin et al., 1999) will be used to screen for depression, which can contribute to false positive results in screening protocols for cognitive impairment.

To determine each participant’s cognitive impairment eligibility, the scoring scheme based on the CCI, QDRS, and NSCT scores summarized in Table 1 will be used. It shows how a research-only diagnosis of normal, SCI, MCI, or ADRD will be used to assess inclusion criteria #3 and exclusion criteria #2 and #3. The decision to use these three cognitive function measures and the scoring scheme in Table 1 was based on recommendations from our ADRD expert, a nationally-recognized neurologist. Because there have not been any validation studies of existing cognitive functioning measures validated for use among NHPI, we decided to use multiple measures of cognitive functioning in research to ensure a more comprehensive (i.e., each measure assesses different aspects of cognitive functioning) and reliable assessment of SCI and MCI. The PHQ2 will assess exclusion criteria #4. Once eligibility is confirmed, participants will be given a standardized form to provide to their physicians requesting their approval to engage in moderate physical activity confirmation of a diagnosis of hypertension, diabetes, and/or hyperlipidemia to address inclusion criteria #4 and #6.

#### Randomization, data collection, and safety monitoring

2.3.3.

After obtaining informed consent and confirming eligibility, participants will be scheduled for baseline data collection. Eligibility screening cognitive data will be used as baseline values for those measures. Aside from these cognitive measures, other clinical and behavioral measures will be administered, which are summarized in Table 2. Data collection will occur in person at the CBO, the participant’s house, or at another convenient location. After completing baseline data collection, participants will be told that they will be contacted as soon as enough people are enrolled to start the next cohort. Based on our prior experience, we expect wait times of under 3 weeks.

The GRT will comprise 16 cohorts with at least 9 people each. After enough eligible individuals are enrolled to populate 2 cohorts, we randomly assign them to either the immediate intervention or wait-list control cohort within that pair. For people in cohorts randomized to the immediate intervention condition, staff will provide instructions for attending the first intervention session. This will be followed by mailed written instructions and a reminder phone call 2–3 days before the first session. For people in cohorts randomized to the wait-list control condition, staff will explain the next steps, including the approximate date of the next data collection. Participants in the wait-list control arm will receive a mailed summary of the next steps, and they will periodically receive phone calls, emails, texts, or mailed letters to maintain contact for scheduling the follow-up data collection. After their study participation is completed, people in the wait-list control cohorts will have the opportunity to receive the intervention, regardless of whether they were retained for the full 12 months of data collection. Assessments take 30–45 min. Each community partner organization keeps its data records and reports the deidentified data to our shared RedCap database.

We will collect baseline and then follow-up at 3, 8, and 12 months after the date of the first hula lesson for the immediate intervention cohort. Because the first phase of our hula intervention involves only hula lessons and our previous study (Kaholokula et al., 2021) found the greatest improvements in blood pressure occurred in these first 3-months, we conducted the first follow-up at 3 months. Our decision to conduct the next follow-up at 8 months is based on a previous study suggesting that it takes at least 8 months of a lifestyle intervention to show significant cognitive improvements in persons at risk for ADRD (Rovner et al., 2018). A 3- and 8-month follow-up also allows us to capture the unique effects of each phase on overall vascular and cognitive risk factors, allowing us to observe where the most change occurs, if any. The final assessment at 12 months (our primary endpoint) will allow us to determine whether the intervention has an effect after active participation in the study has concluded.

Data collection protocols will be identical for all participants to prevent bias that could occur if data collection methods differ by study condition. To schedule the follow-up visits, participants will be contacted about 1 month before the target visit date to remind them of the upcoming data collection and inform them that staff will be making contact for scheduling. Study staff will subsequently make up to 3 attempts to contact each participant by telephone, text, or email, according to preferences specified at enrollment. If these attempts are unsuccessful, a follow-up call or letter will be mailed informing the participant that we have been trying to reach them and providing contact information to schedule the appointment. At this time, we will also reach out to alternative contacts (family or friends) using information provided by the participant at enrollment. If we have been unable to schedule the follow-up by the target date, participants will be mailed a final letter informing them that the visit will be considered as skipped. For people who miss the 3- or 6-month visit, this letter will also explain that they are still eligible for future follow-up.

All participants will receive $25 as an incentive for each data collection visit. Compensation will be provided in the form of gift cards, typically for local gas or grocery outlets, but details will be determined in consultation with stakeholders at each CBO. Participants who miss any data collection visit will have the chance to reschedule and will receive full compensation if the visit is completed within one month of the target date.

Trained research staff will conduct intermittent fidelity checks to record the degree to which *Kumu Hula* and community peer educators follow the standardized protocols, with booster training offered as needed. Attendance at hula lessons will be tracked. A Data and Safety Monitoring Plan and Board will ensure participant safety and study data validity and integrity.

#### Measures

2.3.4.

Cognitive function will be measured by the CCI, NSCT, and QDRS. Also, Cognivue,^®^ a computerized tool for the automated assessment of cognitive functioning that is not dependent on traditional question-and-answer testing, will be administered (Cahn-Hidalgo et al., 2020). SCI and MCI will be defined as described earlier using a combination of CCI, NSCT, and QDRS scores. The CCI will measure our primary outcome for subjective cognitive complaints. The CCI, NSCT, QDRS and Cognivue^®^ will measure our outcomes of change in cognitive performance. CCI, NSCT, and QDRS will be analyzed individually as continuous and categorical variables to indicate improvement, stability, or deterioration. Change in SCI or MCI will be defined similar to eligibility criteria (Table 1). For people with SCI at enrollment, worsening of condition (versus stability) will be defined as declining to MCI by demonstration of an objective decline in cognitive function but with activities of daily living still within the normal range and QDRS scores 2.0–5.5. For individuals with SCI or MCI at enrollment, the worsening of condition will also include transition to ADRD, defined by an objective decline in cognitive function, interference with daily activities, and a QDRS score ≥6. While no medical care is provided as part of this project, individuals identified as MCI or transitioning from SCI to MCI will be offered referrals to a local neurologist. A Functional Activity Questionnaire developed by one of our investigators will be administered to participants to assess activities related to independent living (e.g., managing medications) and used to evaluate early-stage disease (Mayo, 2016).

For vascular risk factors, blood cholesterol and hemoglobin A1c data will be collected from a small drop of capillary blood from a finger stick using the A1CNow^®^^+^ and CardioChek Plus Analyzer. Hemoglobin A1c reflects overall blood glucose levels over the past 2–3 months and will be measured for all participants regardless of previous diabetes diagnosis. Values will be categorized as normal (<6.0 %), diabetic in good control (6.0 %–6.9 %), diabetic in fair control (7.0 %–7.9 %), or diabetic in poor control (≥8.0 %). Participants without a pre-existing diabetes diagnosis whose hemoglobin A1c is measured between 6 % and 7.9 % will be asked to see their primary care provider as soon as possible or immediately seek medical treatment for those above 8 %. Systolic and diastolic blood pressures (mmHg) will be collected with a portable automatic blood pressure device (Omron©HEM-907XL, Omron Healthcare). Standardized protocols involve taking 3 measurements, using the last 2 measures to obtain the average systolic and diastolic blood pressure for each participant (Pickering et al., 2005). Hypertensive status will be defined as blood pressure ≥130/80 mmHg. People with a blood pressure of ≥180/120 mmHg will be referred for immediate medical treatment. Weight will be measured by an electronic scale (Seca 876) that reliably captured weight change in our prior studies. Height in cm will be collected using a stadiometer (Seca 213). Body mass index will be calculated as kg/m^2^, and obesity will be defined as a body mass index ≥30. These methods and tools for collecting clinical data have been successfully used with NHPI participants in other studies (Kaholokula et al., 2014, 2017, & 2021).

For lifestyle behaviors and psychosocial factors, the 3-item Physical Activity Questionnaire will be used to assess exercise frequency during the past month, which asks about moderate activity level, vigorous activity level, and change in activity, and used previously with NHPI (Kaholokula et al., 2014). The validated Cognitive and Leisure Activity Scale is an inventory of common activities that have been well-established as beneficial in older populations (Galvin et al., 2021). The scale assesses engagement with cognitive and physical activities with a 16-item questionnaire. A 39-item version of the Eating Habits Questionnaire will estimate the average daily fat in diet (Kristal et al., 1994), which has been used previously with NHPI (Kaholokula et al., 2014). A health behavior survey will capture the frequency and duration of tobacco and alcohol use. The Global Sleep Assessment Questionnaire includes items on bed and wake times, sleep latency, and snoring, among other factors (Roth et al., 2002). IADL will be measured with the Functional Activity Questionnaire (Pfeffer et al., 1982). Depression symptoms will be measured by the 10-item CES-D. Scores will be evaluated on a continuous scale (range 0–30), and as a binary indicator of scores ≥10.

Demographic data collected will include date of birth, biological sex, marital status, employment status, educational attainment, occupation, specific NHPI ancestry, and prior hula experience. Family history of dementia will be assessed using standard protocols that ask about having at least 1 first-degree relative diagnosed with ADRD and whether a physician had established the diagnosis of ADRD in the first-degree relative following a diagnostic evaluation (Donix et al., 2012). Bilingualism will be assessed by asking: “What is the language you were exposed to from birth?” “What language do you primarily speak at home?” and “How many languages do you speak fluently?” Neighborhood safety will be assessed with an adapted 13-item scale on walking environment, safety, and social cohesion (Mujahid et al., 2007). Social habits around recreational drinking and drug use were assessed with a modified scale from the PILI ‘Ohana Project (Kaholokula et al., 2014).

Consistent with our CBPR approach, our community partners wanted to reduce the physical and mental burden on the older NHPI adults by lessening the overall assessment duration (i.e., no longer than 1 h) and the number of assessment measures. Thus, we limited the assessments to only capturing our primary (i.e., vascular risk factors for ADRD and subjective cognitive complaints) and secondary outcomes (i.e., other measures of cognitive performance, physical function, and mental health) to answer our primary research aim, which was to determine the intervention effect on improving vascular and cognitive risk factors of ADRD. We also include measures to capture potential mediators depicted in Fig. 2, such as depression, substance use, sleep behaviors, diet, and physical activity.

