#### Statistical analysis and power

2.3.5.

We will first calculate descriptive statistics and generate visual plots to assess the balance of individual-level covariates between intervention and control groups at baseline and to depict informative cross-sectional and longitudinal patterns in the data. For the intervention effects on vascular health and cognitive function, we will analyze the data using group randomized trial methods that account for clustering of individuals within intervention cohorts and appropriately modify the degrees of freedom (Murray et al., 2004). Primary outcomes are blood pressure, hemoglobin A1c, blood lipids, and body-mass-index for vascular risk factors, CCI for subjective memory complaints, QDRS for attention and memory scores for cognitive function, and the Cognivue^®^ for general cognition. CCI and QDRS will be analyzed as continuous and dichotomous variables. QDRS will be dichotomized at the recommended cut-off scores of 2–5.5 for mild and ≥ 6 moderate/severe impairment (Maruff et al., 2013). CCI will use the recommended cut-off scores for SCI as 6 ≤ and less than 6 as normal cognitive function. Secondary outcomes will be other measures of vascular risk factors, cognitive function, and other variables relevant to ADRD risk. Separate regression models will be fit for each of the outcomes with no adjustment for multiple comparisons.

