## Discussion

4.

Given the high risk of ADRD among NHPI, our ʻIKE Kūpuna project seeks to reduce this risk by designing and testing a novel, culturally grounded lifestyle intervention among NHPI with the vascular risk factors for ADHD and very early signs of cognitive problems. Our project features several important innovations. First, we test an authentic cultural practice as a paradigm-shifting health promotion and disease prevention strategy aimed at preventing cognitive decline in NHPI, a high-risk population that has been largely excluded from ADRD research. Secondly, our hula program seeks to promote healthy lifestyles consistent with NHPI values and aspirations and thus likely to lead to sustainable behavior change for at-risk NHPI individuals. Finally, the use of a culturally grounded intervention that leverages a prevalent and assessable cultural practice, such as hula, can be naturally sustainable in NHPI communities with existing resources.

A strength of this project is our use of hula, a traditional cultural practice, for ADRD prevention in NHPI. This approach has a strong theoretical foundation supported by preliminary data. Its popularity and accessibility will ensure that this adapted hula-based intervention is appealing and sustainable. The primary requirement of our programs is the presence of a trained kumu, and there are hundreds of kumu present on a global level (Mele.com, 2010). Another strength is the inclusion of both subjective and objective cognitive measurements. Considering the mild complaints many participants will report, relying solely on cognitive performance could miss important improvements in both symptoms and longer-term outcomes among individuals with SCI.

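### The QDRS, a self-report scale, is labelled a measure of cognitive performance and function, so a self-rated improvement alone could be reported as objective benefit

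*Protocol article*

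**What the plan says.** Section 2.3.2 (Informed consent and screening) introduces the CCI as "a subjective measure of cognitive impairment" and the QDRS as "a validated staging assessment for ADRD of participants’ self-reported ratings of cognitive function", with ratings of change from prior abilities in 10 domains. The same section describes the NSCT as a timed 90-second task covering attention, planning and set-switching.

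Section 2.3.4 (Measures) opens with "Cognitive function will be measured by the CCI, NSCT, and QDRS" and adds Cognivue, a computerised test. It names the CCI as the primary outcome for subjective complaints. The next sentence says that CCI, NSCT, QDRS and Cognivue together "will measure our outcomes of change in cognitive performance".

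Section 2.3.5 (Statistical analysis and power) lists the primary outcomes. The CCI is there for subjective memory complaints and Cognivue for general cognition. The QDRS entry reads "QDRS for attention and memory scores for cognitive function". The NSCT is not named in that list.

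Sections 1.7 and 3 expect benefit on subjective complaints and, separately, on objective cognitive function. Section 4 relies on the distinction: "Another strength is the inclusion of both subjective and objective cognitive measurements".

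**The concern.** By the article's own description the QDRS records what participants say about their cognition. It does not test them. Calling it a measure of performance, and a primary source of attention and memory scores, contradicts section 2.3.2 and blurs the line between two hypotheses that the trial keeps apart.

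The label matters because of the design. The comparator is a wait-list, participants are told which condition their cohort is in (2.3.3), community staff are to be trained both to deliver the intervention and to carry out the assessments (2.1.3), and no blinding is described. Self-ratings are open to expectation in that setting. Each outcome has its own model with no multiplicity adjustment (2.3.5), and nothing says which instruments carry the claim about objective function. A favourable QDRS result could be presented as better cognitive function on its own.

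**Working it through.** **Instruments against constructs**

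| Instrument | What 2.3.2 or 2.3.4 says it is | Role in 2.3.4 | Role among primaries in 2.3.5 |
|---|---|---|---|
| CCI | Subjective measure | Subjective complaints, and also performance | Subjective memory complaints |
| QDRS | Self-reported ratings | Performance | Attention, memory, cognitive function |
| NSCT | Timed task | Performance | Not named |
| Cognivue | Computerised test | Performance | General cognition |

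Two of the four instruments under performance are self-report. The CCI is correctly placed elsewhere in 2.3.4 and in 2.3.5. The QDRS is labelled as performance or function in both places and as self-report in neither. The QDRS domains named in 2.3.2 include memory, but as a rating of change; the attention task described there is the NSCT.

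**The plan's own figure**

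Section 2.3.5 gives 80% power for a standardised effect of 0.38 (within-person correlation r = 0.8) to 0.56 (r = 0.5), for Cognivue, CCI and NSCT. Inputs from that section: 8 groups per arm, 9 per group, about 80% retention (9 × 0.8 = 7.2, taken as m = 7), intra-cohort correlation 0.01, alpha 0.05 (two-sided assumed). The closest match found uses baseline adjustment and 7 degrees of freedom:

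MDE = (t.975 + t.80) × √[2(1 − r²)(1 + (m − 1) × 0.01)/(8m)]

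- t.975 + t.80 = 2.365 + 0.896 = 3.261
- r = 0.8: √(2 × 0.36 × 1.06/56) = 0.1167, and 3.261 × 0.1167 = 0.381
- r = 0.5: √(2 × 0.75 × 1.06/56) = 0.1685, and 3.261 × 0.1685 = 0.549

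This is close to the stated 0.38 and 0.56. The calculator's settings are not given, so the match is an inference. The figure itself is not in dispute.

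**Illustration of a reporting shift**

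Assume no true effect and a pure reporting difference of 0.1, 0.2 or 0.3 SD. These sizes are assumptions; the article gives none. Take the standard error implied by the stated effects with 14 degrees of freedom (16 groups − 2):

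- t.975 + t.80 = 2.145 + 0.868 = 3.013
- SE = 0.38/3.013 = 0.126, or 0.56/3.013 = 0.186
- Chance of a favourable significant result = P(noncentral t with 14 df and noncentrality shift/SE exceeds 2.145)

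| Assumed shift | r = 0.8 | r = 0.5 |
|---|---|---|
| 0 | 2.5% | 2.5% |
| 0.1 SD | 11% | 7% |
| 0.2 SD | 32% | 17% |
| 0.3 SD | 60% | 32% |

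With 7 degrees of freedom each entry moves by less than half a percentage point. Applying these standard errors to the QDRS is a further assumption, because the stated effect sizes do not cover it.

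**The case against.** The strongest reply is that this is loose wording with little consequence. Section 2.3.2 states openly that the QDRS is self-reported, and nowhere is it called objective. CCI, NSCT and QDRS are analysed individually, and Table 2 collects all four instruments at 8 and 12 months. For worsening, section 2.3.4 asks for an objective decline as well as a QDRS band. Which instrument supports which claim is often settled in a full protocol or analysis plan that is not shown.

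Much of this stands, and it rules out several stronger readings that a reader might infer:

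- That both scales are equally misassigned. They are not; the CCI is named twice as the subjective outcome.
- That a drop in CCI and QDRS would by itself meet a written success criterion for cognitive function. No composite or any-of-four rule exists.
- That the trial could not tell feeling better from performing better. It could: flat NSCT and Cognivue results would be visible beside the QDRS.

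What does not stand is that separate analysis cures the label. Nothing requires the performance tests to agree before improved function is claimed. The objective-decline condition governs only the worsening category, not the continuous and dichotomous QDRS analyses in 2.3.5. Section 2.3.4 also ties change in status to Table 1, where a QDRS of 2–5.5 gives MCI with any NSCT score. Nor is this merely detail left to another document: the article makes a statement that conflicts with its own description of the scale.

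**Conclusion.** The point holds for the QDRS, and for the CCI only as a matter of consistency. One primary outcome in 2.3.5 is described as a measure of attention, memory and cognitive function although it is self-rated, and the performance list in 2.3.4 repeats the error. The consequence is a risk of interpretation: a favourable QDRS result alone could be offered as evidence for the objective-function hypothesis in a trial whose participants know their arm. That the trial is unblinded is inferred from the wait-list design and the absence of any described blinding.

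The 7% to 60% range should not be read as the size of this defect. It rests on assumed shifts and on effect sizes stated for other instruments. It would apply to any self-reported outcome in this design, including a correctly labelled CCI, and the correction leaves it unchanged. No sample size or power figure needs revising.

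A reader might also infer that the attention-and-memory phrase was meant for the NSCT. The article does not support that: its NSCT description covers attention but not memory, while the QDRS has a memory domain.

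**What to change.** In 2.3.4 and 2.3.5, label the QDRS, and consistently the CCI, as self-reported outcomes, and take both out of the list of performance measures. State that any claim about objective cognitive function rests on the performance-based measures, Cognivue and NSCT. Correct the attention-and-memory description of the QDRS in 2.3.5 after the authors confirm which instrument or score was intended. Do not add the NSCT to the primary outcomes by default, since that would change the endpoint set and not just its wording.

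All four instruments are already scheduled, so no data collection changes. The cost is that a favourable QDRS result can no longer count as evidence of objective function; it remains a legitimate self-reported outcome.
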